## Abstract

**Background:**

Smoking is the leading preventable cause of death in the United States, but evidence-based smoking cessation therapy is underutilized. Financial incentive strategies represent an innovative approach for increasing the use of counseling and pharmacotherapy. If effective, they could supplement or supplant resource-intensive policy options, particularly in populations for whom smoking has substantial societal costs. FIESTA (Financial IncEntives for Smoking TreAtment) will randomize hospitalized smokers to receive usual smoking cessation care alone or usual smoking care augmented with financial incentives. We aim to compare the impact of these two strategies on 1) smoking abstinence, 2) use of counseling and nicotine replacement therapy, and 3) quality of life of participants. We also will evaluate the short-term and long-term return on the investment of incentives. The FIESTA Oral Microbiome Substudy will compare the oral microbiome of smokers and nonsmokers to longitudinally assess whether smoking cessation changes oral microbiome composition.

**Methods:**

We will enroll 182 inpatient participants from the Manhattan campus of the Veterans Affairs New York Harbor Healthcare System. All participants receive enhanced usual care, including screening for tobacco use, counseling while hospitalized, access to nicotine replacement therapy, and referral to a state Quitline. Patients in the financial incentive arm receive enhanced usual care and up to $550 for participating in the New York Smoker’s Quitline, using nicotine replacement therapy (NRT), and achieving biochemically confirmed smoking cessation at 2 months and 6 months. In the microbiome substudy, we enroll nonsmoking control participants matched to each recruited smoker’s hospital ward, sex, age, diabetes status, and antibiotic use. After discharge, participants are asked to complete periodic phone interviews at 2 weeks, 2 months, 6 months, and 12 months and provide expired carbon monoxide and saliva samples at 2 months, 6 months, and 12 months for cotinine testing and oral microbiome analysis.

**Discussion:**

The incentive interventions of FIESTA may benefit hospitalized smokers, an objective made all the more critical because smoking rates among hospitalized patients are higher than those in the general population. Moreover, the focus of FIESTA on evidence-based therapy and bioconfirmed smoking cessation can help guide policy efforts to reduce smoking-related healthcare costs in populations with high rates of tobacco use and costly illnesses.

**Trial registration:**

ClinicalTrials.gov, NCT02506829. Registered on 1 July 2014.

**Electronic supplementary material:**

The online version of this article (10.1186/s13063-018-3003-y) contains supplementary material, which is available to authorized users.

## Background

Smoking is the leading preventable cause of death and disease in the United States [1], and most adults who continue to smoke are disproportionately low-income or have no college education [2]. While 70% of smokers express the desire to quit [3], only 25% of those individuals seek assistance with smoking cessation and an even smaller proportion use evidence-based methods [4], such as behavioral counseling or pharmacotherapy [5]. Among hospitalized patients, tobacco dependence treatment is particularly critical because persistent smoking increases the risk of future smoking-related illnesses, such as coronary heart disease, cerebrovascular disease, emphysema, and cancer [1, 6].

Financial incentives for smoking cessation may be an effective strategy for increasing the use of evidence-based cessation therapy among hospitalized patients [7–10]. Based on principles from microeconomic theory, financial incentives influence individual behavior and decision-making because individuals are motivated by the prospect of welfare gains. While evidence is mixed, some incentive interventions have been effective in the treatment of obesity [11], diabetes [12], and smoking at the worksite [9]. Incentives may be particularly effective when designed to leverage concepts from behavioral economics, such as immediacy of payments and framing of missed payments with regret aversion [7, 8, 13–17]. If effective, financial incentive programs could supplement or supplant other policy options for smoking cessation, particularly in populations for whom smoking has substantial societal costs. In addition, because health insurers are increasingly adopting bundled payment systems and smokers generally incur high healthcare costs [8, 13, 18], financial incentives may be sustainable due to their potentially favorable return on investment [14, 15]. The effectiveness of financial incentives for increasing smoking cessation among hospitalized patients is unknown.

In addition to the potential effectiveness of incentives for smoking cessation, another scientific area of growing relevance to smokers is the oral microbiome. Smokers have higher levels of oral mutagens and carcinogens, and this may contribute to their increased risk of oral cancer. It is also known that quitting smoking reduces the risk of developing oral cancer [19]. Recent research has suggested that a mechanism explaining the association of smoking and oral cancer may involve activation of carcinogens deposited through smoking by oral bacteria [20]. However, little is known about how smoking cessation affects the oral microbiome of smokers.

### Objectives

The primary objective of the Financial IncEntives for Smoking TreAtment (FIESTA) trial is to compare the effects of two approaches for smoking cessation—financial incentives plus enhanced usual care versus enhanced usual care alone—on smoking abstinence, use of evidenced-based therapy, and quality of life. The second objective is to estimate the short-term and long-term return on investment of using financial incentives to promote smoking cessation. In addition, the FIESTA Oral Microbiome Substudy will be conducted to determine whether smoking cessation changes the oral microbiome composition of smokers.

We hypothesize that participants in the financial incentives arm will experience higher rates of smoking cessation, improved quality of life, and lower rates of financial distress, and that these gains will be associated with a favorable return on investment. We also hypothesize that patients experiencing greater financial distress at baseline will be more likely to stop smoking in response to financial incentives. Our oral microbiome hypothesis is that smoking cessation will lead to changes in the microbiome that increase its similarity to the microbiome of nonsmokers.

## Methods/design

### Overall design

The trial is sponsored by the Robert Wood Johnson Foundation. We will enroll 182 inpatient participants from the Manhattan campus of the Veterans Affairs (VA) New York Harbor Healthcare System. After conducting a baseline survey of the sociodemographic and clinical characteristics of participants and administering a Stages of Change questionnaire, smokers are randomized to the financial incentives plus enhanced usual care arm or the enhanced usual care alone arm with an allocation ratio of 1:1. All participants receive enhanced usual care, which includes tobacco use screening, counseling while hospitalized, hospital-directed educational materials on quitting smoking, nicotine replacement therapy (NRT) at the discretion of inpatient healthcare providers, and referral to a state Quitline (this component represents the enhancement). The components of enhanced usual care were selected based on prior evidence for effective smoking cessation interventions. In addition to enhanced usual care, smokers who are randomized to the financial incentives arm are also eligible to receive up to $550 for participating in counseling (both community-based counseling and state Quitline counseling), using smoking cessation pharmacotherapy, and biochemically confirmed smoking cessation at 2 months and 6 months. The incentive schedule is summarized in Table 1, and Figs. 1 and 2 display brochures provided to participants in the enhanced usual care arm or the financial incentives plus enhanced usual care arm.

**Table 1 Tab1:** Schedule of financial incentives

Activity	Time point	Incentive
Speaking with a coach from the NYS Smoker’s Quitline	2 weeks	$50
Completion of community-based smoking cessation program	2 weeks	$50
Use of pharmacotherapy for smoking cessation	2 weeks	$50
Smoking cessation (self-report + salivary cotinine)	2 months	$150
Smoking cessation (self-report + salivary cotinine)	6 months	$250

**Fig. 1 Fig1:**
[figure not shown]
Brochure provided to participants in enhanced usual care arm summarizing time points for follow-up and compensation. NRT nicotine replacement therapy, VA Veteran’s Affairs

**Fig. 2 Fig2:**
[figure not shown]
Brochure provided to participants in financial incentives arm summarizing time points for follow-up and compensation. NRT nicotine replacement therapy, VA Veteran’s Affairs

After discharge, smokers are asked to complete periodic phone interviews for 12 months to assess patient-reported smoking cessation, use of evidence-based cessation interventions, and quality of life. All participants are also asked to provide saliva samples for 12 months for both cotinine testing and oral microbiome analysis. Smoking status at 6 months, as determined by salivary cotinine analysis, is used to determine whether a patient is considered a persistent smoker or a past smoker because rates of recidivism are low after 6 months [21], while many patients who quit smoking immediately after being hospitalized soon relapse [16]. An outline of enrollment, intervention, and assessment can be found in the SPIRIT figure (Fig. 3) and SPIRIT checklist (Additional file 1).

**Fig. 3 Fig3:**
[figure not shown]
Schedule for enrollment, interventions, and assessments (SPIRIT figure)

### Study population

The VA Hospital in Manhattan is a New York University (NYU) School of Medicine-affiliated teaching facility. The institution predominately serves low-income veterans that reside in Manhattan or its surrounding regions. The low socioeconomic status of most participants in this trial may limit the generalizability of our findings to other socioeconomic groups within the United States and elsewhere. Each year, approximately 4000 patients are admitted to its medical and surgical services, while another approximately 1000 patients are admitted to its psychiatry service. Roughly 60% of hospitalized patients at the Manhattan VA are Caucasian, 31% are African American, and 17% are Hispanic or Latino. Furthermore, about 61% of these patients have only a high school education or less. The institution routinely cares for patients with acute myocardial infarction, congestive heart failure, pneumonia, and chronic obstructive pulmonary disease—all conditions associated with smoking.

### Eligibility criteria

The criteria for hospitalized patients considered for enrollment in FIESTA are: 1) ≥ 18 years of age; 2) smoked tobacco during the 30 days prior to hospitalization; 3) possess an active US phone number; 5) not pregnant or breastfeeding; 6) reside in the NYC area or have the ability to return to the Manhattan VA for at least 1 year; 7) contemplating smoking cessation as assessed by readiness to quit [22]; and 8) able to provide consent in English. Potential participants are excluded if they: 1) use smokeless tobacco only; 2) are pregnant or breastfeeding; 3) anticipate to be discharged to an institution (i.e., a nursing home or long-term care facility) at which the patient will not have control over smoking rules; or 4) are unable to provide informed consent.

### Recruitment

The Veterans Information Systems and Technology Architecture (VISTA) program is used to gather information from the Electronic Health Record (EHR) system (specifically from nursing or physician admission assessments) to identify hospitalized smokers who are eligible for participation. Each day, an EHR-generated current smokers list is created and used to recruit. Staff approach every potential participant to describe the study, assess eligibility through the completion of a screener, offer enrollment if eligible, complete a Research Consent Form and HIPAA Release Form, and conduct a baseline survey and saliva collection. All electronic data are kept in a password-protected and encrypted database (REDCap) and each participant is assigned a study ID number to separate their identifiable information from the study records. Potential participants are also informed that their participation is completely voluntary, and their consent can be withdrawn at any time by providing staff with a letter requesting they no longer be contacted.

The FIESTA Oral Microbiome Substudy will enroll both smokers and hospitalized nonsmokers as controls. For each smoker enrolled in FIESTA, staff will attempt to recruit a matched nonsmoker using VISTA and electronic chart review. Nonsmokers are matched based on: 1) age within 10 years (if a match is identified in the first 30 days after enrollment of the corresponding FIESTA participant) or within 20 years (after the first 30 days); 2) sex; 3) ward location; 4) antibiotic use; and 5) diabetes status. We will relax the matching criterion based on diabetic status if we are otherwise unable to identify a match.

The Computerized Patient Record System (CPRS) is used to track the discharge information of participants and to complete a chart abstraction 1 week postdischarge. After discharge, smokers are referred to a state Quitline (either New York or New Jersey) by research staff and later contacted by a state Quitline counselor to discuss NRT, plans and strategies for quitting, and other available smoking cessation resources.

### Randomization

Smokers are randomized in a 1:1 ratio to either financial incentives plus enhanced usual care or enhanced usual care alone. We employ a computer-generated block randomization design. Research staff implement the allocation sequence using numbered, sealed envelopes that are opened during participant enrollment. Because of the nature of the intervention, participants are not blind to their randomization into either the financial incentives plus enhanced usual care or enhanced usual care groups.

### Intervention

Smokers who are randomized into the financial incentives plus enhanced usual care arm are eligible to receive $550 for participating in counseling, using NRT, and achieving biochemically confirmed smoking cessation at 2 months and 6 months (see Table 1). All participants are compensated in US dollars (USD) using ClinCards, a secure prepaid debit card system.

Research staff members are extensively trained in the teach-back method in which study participants are asked to repeat task-specific directions to staff to confirm understanding. The teach-back method has been shown to improve instruction retention in patients postdischarge [23]. This instructional technique will be incorporated into the FIESTA protocol to ensure that participants understand not only the study aims and timeline, but have also comprehended the targets for which they are being incentivized.

### Data collection and measurement of smoking cessation outcomes

Participants are asked to complete an in-person survey at enrollment and four follow-up interviews by phone at 2 weeks, 2 months, 6 months, and 12 months. Each participant receives $20 after completing surveys at each of the follow-up time points. Each participant is also asked to provide saliva samples at enrollment and at 2 months, 6 months, and 12 months, for which we provide a $50 payment to increase participation rates. The baseline and follow-up surveys are similar in content and assess: 1) sociodemographic characteristics (i.e., demographics, contact information, race/ethnicity, health literacy, exercise habits, and nutrition habits) [24]; 2) smoking history (i.e., smoking habits and home environment using questions adapted from the California Tobacco Survey [25], nicotine dependence using questions adapted from the Heaviness of Smoking Index [26], and smoking cessation services received); 3) preference for incentive design (goal-directed versus outcome-based); 4) participant health (i.e., health status using the Veterans RAND 12-item Health Survey [27] and the EuroQol-5D [28–30] to assess physical and mental functioning, alcohol-use using the AUDIT-C [31, 32], marijuana use using the ASSIST, substance use using the self-administered Substance Use Brief Screen [33], and depression using the PHQ-2 [34]); and 5) health services utilization in the prior 6 months. The baseline and follow-up surveys also measure treatment outcomes (i.e., 7-day and 30-day point prevalence for smoking cessation, quit attempts, reduction in daily smoking, changes in readiness to quit, and use of NRT and Quitline counseling).

We collect saliva samples from each participant at baseline, 2 months, 6 months, and 12 months. The sample is analyzed for cotinine—a biomarker that reflects exposure to nicotine—using NicAlert kits to bioconfirm smoking cessation, and the sample is also used to characterize the oral microbiome. All participants also undergo a carbon monoxide breath test at every saliva collection. In addition, we ask each participant if they have taken antibiotics in the 7 days prior to saliva collection or used NRT, e-cigarettes, or other forms of tobacco in the 7 days prior to saliva collection. At 2 months, if a participant reports tobacco abstinence, but is still using NRT and the cotinine testing results in a value between 10 and 99 ng/mL, we use the carbon monoxide breath test for biochemical validation. Research staff collect all saliva samples in public locations convenient to the patient or at the Manhattan VA.

Research coordinators periodically audit study procedures every 3 to 6 months to ensure implementation fidelity and adherence to the study protocol. Routine re-training of research staff to reinforce study procedures is performed every 6 to 9 months. This process is performed independently of the investigators, but impressions of study staff performance and feedback from re-training exercises are shared with the principal investigators.

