### Analytic plan

The primary outcome in this trial is the smoking cessation rate at 6 months. Secondary outcomes in this trial include: 1) financial distress and security; 2) subjective social status; 3) other substance use including alcohol; and 4) quality of life. Chi-squared tests, *t* tests, and nonparametric tests will be used to compare baseline characteristics of patients to assess balance between the two study arms. Multivariate analyses for longitudinal data will include difference-in-difference models and Cox proportional hazard models, and these models will include patient-level variables, area-based socioeconomic factors, and hospital variables as covariates.

For the economic evaluation, we will estimate the return on investment of financial incentives intervention from the perspective of the healthcare system (hospitalizations, ambulatory care, and medications) on a per-patient basis. Costs will be determined by: 1) multiplying employee wages (based on United States Bureau of Labor Statistics values) [35] by the estimated time these personnel spend on smoking cessation care; 2) using the Red Book to estimate NRT and other medication costs (based on average wholesale prices) [36]; and 3) estimating bulk purchase prices for other physical materials provided to smokers. The return on investment will then be estimated using the difference between the value of financial incentives provided to smokers and the incremental healthcare costs or savings, comparing the financial incentives plus enhanced usual care arm to the enhanced usual care alone arm.

We will also estimate the cost-effectiveness of the financial incentives intervention using the ratio of the difference in costs between the intervention group and control group to the difference in quality of life and smoking cessation rates between the intervention and control groups [37]. We will perform nonparametric bootstrapping with 1000 random samples to estimate confidence intervals (CIs) for the cost-effectiveness ratios and we will use the bias-corrected percentile method described by Efron and others [38–40]. We will consider recidivism rates of participants when estimating the cost-effectiveness of the interventions in this trial. Specifically, we anticipate that recidivism will reduce cost-effectiveness by reducing the incremental benefits of the intervention.

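### The economic formulas leave out, or largely cancel, the cost of verifying abstinence, which the incentive programme must bear and enhanced usual care does not

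*Protocol article*

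**What the plan says.** All references are to the protocol article.

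- **Payment condition.** In Table 1 (Overall design) the $150 payment at 2 months and the $250 payment at 6 months are each tied to "Smoking cessation (self-report + salivary cotinine". The Intervention section repeats the condition: "achieving biochemically confirmed smoking cessation at 2 months and 6 months (see Table 1".
- **Comparator.** Overall design defines what both arms get as care: "All participants receive enhanced usual care, which includes tobacco use screening, counseling while hospitalized, hospital-directed educational materials on quitting smoking", followed by nicotine replacement at the providers' discretion and Quitline referral. Biochemical testing is not part of it.
- **Testing in the trial.** Data collection and measurement of smoking cessation outcomes has everyone tested, in both arms: "We collect saliva samples from each participant at baseline, 2 months, 6 months, and 12 months" and "All participants also undergo a carbon monoxide breath test at every saliva collection". The work is done by trial personnel, partly off site: "Research staff collect all saliva samples in public locations convenient to the patient or at the Manhattan VA".
- **Economic formulas.** The Analytic plan costs three things: wages multiplied by the "estimated time these personnel spend on smoking cessation care", medications, and physical materials given to smokers. The return on investment sets the amount paid out in incentives against incremental healthcare costs or savings, "comparing the financial incentives plus enhanced usual care arm to the enhanced usual care alone arm". Cost-effectiveness is the between-arm difference in costs divided by the difference in quality of life and in cessation.

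**The concern.** A health system that adopted this programme could not pay the two cessation sums without testing the people who claim them. It would need a kit, in some cases a carbon monoxide reading, and staff time to meet the patient. A health system offering enhanced usual care alone would carry none of this. Verification is therefore a running cost of the incentive strategy and belongs on its side of the ledger.

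The stated formulas do not put it there. The return on investment is the second objective of the trial, and the Discussion presents the economic evaluation as the answer to whether incentives are financially sustainable. An omission that always points the same way, and that more patients would not reduce, matters for that objective.

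**Working it through.** **1. The stated figure.** Table 1 adds up: 3 × $50 + $150 + $250 = $550. The part that needs biochemical confirmation is $150 + $250 = $400. The document gives no unit cost, return on investment or cost-effectiveness figure to reproduce.

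**2. Return on investment.** The only programme input named is the incentives paid. Verification has no place on the investment side, whatever is done with controls. The other side is a between-arm difference in healthcare costs, from a perspective described as hospitalizations, ambulatory care and medications. If a test visit were counted there, step 3 would apply to it.

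**3. Cost-effectiveness numerator.** If verification is not costed, it contributes nothing. If it is costed in both arms at v dollars per visit, with attendance a1 (incentives) and a0 (control) at two paid visits, the difference is 2v(a1 − a0).

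The Sample size section expects 10–15% loss at 6 months, so attendance of 85–90% is in line with the plan; 80% is an added assumption.

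- Equal attendance: 2v × 0 = $0.
- 90% against 85%: 0.05/0.90 = 5.6% of the cost of testing every incentive-arm attender.
- 90% against 80%: 0.10/0.90 = 11.1%.

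A real programme would test only those claiming abstinence. Against that smaller cost, with 52.5% claiming, the captured share is 0.05/0.525 = 9.5% or 0.10/0.525 = 19.0%. With 30% claiming and the 10-point gap it reaches 0.10/0.30 = 33%. Most of the cost is lost in each case.

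**4. Size of the omitted cost (all inputs assumed).** Cost per incentive-arm patient = 2 visits × share claiming abstinence × v.

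- 30% claiming: 2 × 0.30 × $10 = $6, to 2 × 0.30 × $100 = $60.
- 52.5% claiming (1.5 times an assumed 35% quit rate): $10.50 to $105.
- 60% claiming: $12 to $120.

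Apart from the low claim share at the cheapest tests, this is roughly $10 to $120.

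**5. Against the payouts (also assumed).** With 60% uptake of each $50 therapy payment and 35% paid at both cessation visits, payout is 0.60 × $150 + 0.35 × $400 = $90 + $140 = $230 per patient. With 52.5% claiming, verification is 10.50/230 = 5% to 105/230 = 46% of that.

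The Sample size section calls a difference of about 20 points clinically substantial. At that difference, incentives alone cost 230/0.20 = $1,150 per extra quitter. Adding verification gives (230 + 10.50)/0.20 = about $1,200, to (230 + 105)/0.20 = $1,675. Healthcare costs and savings are left out of this illustration.

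**The case against.** The strongest reply is that the Analytic plan is a condensed account. It estimates care inputs and does not tally trial spending. Sampling controls to measure the outcome is not obviously smoking cessation care, while testing that a payment depends on could be. On that reading verification would be charged to the incentive arm only, nothing would cancel, and the allocation rule would be detail left to a fuller economic plan.

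Part of this stands. No sentence says that research testing will be costed in the control arm, so cancellation is one possible outcome and not a stated rule. But no sentence charges verification to the incentive arm either, and the favourable reading has no place on the investment side of the return on investment, which is written out with incentives as its only programme term. That is a formula the article states, not a missing detail.

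A reader might also infer two stronger claims that the document does not support:

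- *That verification is set to exactly zero in both measures because controls are tested.* Control testing can explain only the cost-effectiveness numerator; in the return on investment the cost is simply not a term. Even in the numerator, zero requires that verification is uncosted or that attendance is equal.
- *That testing everyone is itself a fault.* Testing both arms alike is sound outcome measurement. The problem lies in the costing.

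**Conclusion.** The point holds for the economic evaluation. As written, the return on investment excludes a cost without which $400 of the $550 cannot be paid. The cost-effectiveness numerator omits that cost or largely cancels it. Both measures are too favourable to incentives.

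The direction follows from the stated formulas. The size does not: unit cost, claim share, quit rate and uptake are all assumptions, and roughly $10 to $120 per incentive-arm patient is an illustration. It would be tempting to conclude that the economic result is materially wrong. The document does not support that, because the healthcare costs and savings that also enter both measures are unknown. The 6-month cessation comparison is not touched.

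**What to change.** In the economic part of the Analytic plan:

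1. Add verification at 2 and 6 months for incentive-arm participants who report abstinence (kit, carbon monoxide test, staff time and travel), together with administration of the payments, to the investment side of the return on investment and to the incentive arm's cost in the cost-effectiveness ratio.
2. Exclude from both arms whatever is done only for research: control-arm testing, testing of incentive-arm participants who report smoking, baseline and 12-month sampling, and the $20 survey and $50 sample payments.
3. State an assumed unit cost per verification, vary it in a sensitivity analysis, and report both measures with and without verification.

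The cost is a few sentences and one unit-cost assumption. Counts can be taken from self-reported abstinence and samples collected, both of which are study data. The article does not say that kits used, staff time or travel are logged, which is why the unit cost needs a range. The downside is a slightly less favourable return on investment and cost per quitter. Enrolment was reported as ongoing, so when the article was written the rule could still be set before follow-up was complete.

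### The carbon monoxide fallback for abstinent NRT users is written for 2 months only, so at the 6-month primary endpoint a cotinine-positive NRT user who has stopped smoking is classed as a smoker

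*Protocol article*

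**What the plan says.** All references are to the protocol article.

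- **Primary outcome (Analytic plan):** "The primary outcome in this trial is the smoking cessation rate at 6 months".
- **Classifier at 6 months (Overall design, text after Fig. 2):** "Smoking status at 6 months, as determined by salivary cotinine analysis, is used to determine whether a patient is considered a persistent smoker". Self-report and CO are not mentioned.
- **Payment criterion at 2 and 6 months (Table 1):** "Smoking cessation (self-report + salivary cotinine". CO is not mentioned.
- **What cotinine measures (Data collection and measurement of smoking cessation outcomes):** "a biomarker that reflects exposure to nicotine".
- **The CO fallback (same section):** its condition opens "At 2 months, if a participant reports tobacco abstinence, but is still using NRT and the cotinine testing results in a value". The band named is 10–99 ng/mL, and for readings inside it the breath test decides.
- **Availability of CO (same section):** "All participants also undergo a carbon monoxide breath test at every saliva collection". Use of NRT, e-cigarettes and other tobacco in the preceding 7 days is also asked in connection with saliva collection.
- **NRT in the trial:** both arms have access to it under enhanced usual care. The incentive arm alone is paid $50 for "Use of pharmacotherapy for smoking cessation", at the 2-week time point (Table 1).

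**The concern.** By the article's own description, cotinine marks nicotine exposure and not smoking as such. A person who has stopped smoking but uses a patch or gum can therefore test positive. The authors foresaw this and wrote a remedy with a time point, a condition and a cotinine range. The remedy is tied to 2 months, which is not the primary time point, and no reason is given for stopping there.

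This is more than detail left to a fuller document: the article states both the rule and the 6-month classifier, and together they give a wrong answer for an identifiable group. What is at stake is the validity of the primary outcome in a trial where both arms are offered NRT. True quitters are removed from the numerator, and the absolute difference between arms, on which the sample size is based, is measured with error. The two descriptions of 6-month status also differ on whether self-report is part of the definition.

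**Working it through.** **Step 1. Who is classified how.** Take a participant who reports no tobacco use, is on NRT, and has cotinine between 10 and 99 ng/mL.

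| Visit | Rule in the article | Result if CO supports abstinence |
|---|---|---|
| 2 months | Cotinine, then CO for this case | Abstinent |
| 6 months (primary) | Cotinine, or self-report plus cotinine | Smoker |
| 12 months | No fallback stated | Not resolved |

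The article gives no separate cotinine cut-off for 6 months. That 10 ng/mL or more counts as positive is inferred from the 10–99 band. The inputs needed to apply the 2-month rule at 6 months (self-report, cotinine, CO, recent NRT use) are all collected.

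**Step 2. The plan's own power figure.** Sample size states at least 80% power for a difference of about 20 points with 91 per arm and α = 0.05. The control rate is not given, so it has to be assumed. I used the pooled-variance normal approximation, two-sided:

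power = Φ{ [ |p₁ − p₀|·√n − 1.96·√(2·p̄·(1 − p̄)) ] / √[ p₀(1 − p₀) + p₁(1 − p₁) ] }

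| Assumed control rate | 5% | 10% | 15% | 20% | 25% | 30% | 35% | 40% |
|---|---|---|---|---|---|---|---|---|
| Power, 91 per arm | 97% | 93% | 88% | 84% | 81% | 79% | 78% | 77% |

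The stated figure holds without loss up to a control rate of about 25%. The present point does not depend on it.

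**Step 3. Effect of the missing fallback.** Let u₀ and u₁ be the shares of true quitters in the control and incentive arms who are classed as smokers because of NRT. Then

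observed rate = true rate × (1 − u).

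If u₀ = u₁ = u, the observed difference is (1 − u) × the true difference. Neither the true rates nor the shares are in the article; all are assumptions.

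Worked case, true rates 20% and 40%, u = 10% in both arms:

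- Observed rates: 0.20 × 0.90 = 0.18 and 0.40 × 0.90 = 0.36, a difference of 18 points.
- No misclassification: [0.20 × √91 − 1.96 × √(2 × 0.30 × 0.70)] / √(0.16 + 0.24) = 1.008, so power is 84.3% (exact binomial for the uncorrected chi-squared test: 84.7%).
- With misclassification: [0.18 × √91 − 1.96 × √(2 × 0.27 × 0.73)] / √(0.1476 + 0.2304) = 0.791, so power is 78.6% (exact: 79.1%).
- With the upper end of the article's expected loss, 15% (91 × 0.85 = 77.35 per arm): 78.0% falls to 71.7%.

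Range for equal shares, true rates 20% and 40%, 91 per arm:

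| u in both arms | Difference | Power |
|---|---|---|
| 0% | 20 points | 84.3% |
| 5% | 19 points | 81.6% |
| 10% | 18 points | 78.6% |
| 20% | 16 points | 71.8% |

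**Step 4. Unequal shares, same true rates.**

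| Control / incentive | Observed rates | Difference | Power |
|---|---|---|---|
| 5% / 10% | 19% / 36% | 17 points | 73.2% |
| 10% / 20% | 18% / 32% | 14 points | 58.9% |
| 20% / 10% | 16% / 36% | 20 points | 87.4% |

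The last row shows that an imbalance in the other direction removes the loss altogether.

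**The case against.** **A fuller rule may exist.** The article condenses a protocol that is not shown, and Table 1 uses the same words for 2 and 6 months although CO is used at 2 months. Table 1 alone therefore does not prove that CO is excluded at 6 months. That stands as far as Table 1 goes. It does not remove the explicit limit to 2 months in the data-collection section, nor the statement in Overall design that 6-month status rests on cotinine.

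**The group may be small.** Perhaps few quitters still use NRT at 6 months, and not every user will test positive. The article gives no figure, so the effect could be close to nil. This limits the size, not the error in the rule.

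**A reader might infer that the error falls mainly on the incentive arm, because that arm is paid to use pharmacotherapy.** The article does not support this. The payment is tied to 2 weeks, both arms have access to NRT and are referred to a Quitline, and only the incentive arm has $250 depending on a cotinine result at 6 months, which is a reason to be off nicotine by then.

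**A reader might also count abstinent e-cigarette users as misclassified at 6 months.** The CO rule names only NRT, so they are outside it at 2 months as well. The question about recent use lists e-cigarettes alongside other forms of tobacco, so treating users as non-abstinent may be intended. The article leaves this unclear; it does not show an error.

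**Finally, the two descriptions of 6-month status might be read as letting a self-reported smoker pass as a quitter on cotinine alone.** The article speaks elsewhere of biochemically confirmed cessation, which presupposes a report to confirm. This is a wording inconsistency to align, not a demonstrated bias.

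**Conclusion.** The point holds in this form: the CO fallback is fixed at a secondary time point and is absent at the primary one. As written, participants who report tobacco abstinence but are cotinine-positive on NRT are smokers in the primary analysis.

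With similar NRT use among quitters in the two arms, the absolute difference shrinks in proportion. Under the assumed 20% and 40% with 10% of quitters affected, the loss is 2 points of difference and about 6 points of power. These figures illustrate and do not estimate: they rest on assumed quit rates, on an assumed share, and on every affected quitter being reclassified. The direction and size of any differential bias between arms cannot be determined from the article.

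**What to change.** 1. Apply the existing rule (reported abstinence, current NRT use, cotinine 10–99 ng/mL, CO validation) at 6 and 12 months as well as at 2 months, using the CO reading already taken at each saliva visit.
2. State one primary-outcome definition, self-report plus biochemical confirmation, and use the same wording in Overall design, Table 1, Data collection and measurement of smoking cessation outcomes, and Analytic plan.
3. State for each time point whether a participant who uses e-cigarettes and no other tobacco counts as abstinent.

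**Cost.** No new measurement is needed, since CO and 7-day NRT and e-cigarette use are already collected. CO has a short detection window, so confirmation is weaker for the few participants verified that way. The change alters how the primary outcome is classified after enrolment began, so it should be documented as an amendment and made before outcome data are analysed.
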